# The PRolaCT studies — a study protocol for a combined randomised clinical trial and observational cohort study design in prolactinoma

**DOI:** 10.1186/s13063-021-05604-y

**Published:** 2021-09-25

**Keywords:** Prolactinoma, Pituitary tumour, Dopamine agonist, Endoscopic transsphenoidal resection, Randomised clinical trial, Observational cohort

## Abstract

**Background:**

First-line treatment for prolactinomas is a medical treatment with dopamine agonists (DAs), which effectively control hyperprolactinaemia in most patients, although post-withdrawal remission rates are approximately 34%. Therefore, many patients require prolonged DA treatment, while side effects negatively impact health-related quality of life (HRQoL). Endoscopic transsphenoidal resection is reserved for patients with severe side effects, or with DA-resistant prolactinoma. Surgery has a good safety profile and high probability of remission and may thus deserve a more prominent place in prolactinoma treatment. The hypothesis for this study is that early or upfront surgical resection is superior to DA treatment both in terms of HRQoL and remission rate in patients with a non-invasive prolactinoma of limited size.

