We hypothesise that endoscopic transsphenoidal adenoma resection as a first-line, or equally valid second-line, treatment is superior to standard care (DA treatment) for patients with a visible prolactinoma of limited size (< 25 mm, no tissue invasion). The primary outcome parameters are (1) HRQoL measured after 12 months of follow-up (i.e. 12 months after randomisation or, in PRolaCT-O, study baseline) and (2) the proportion of patients in remission at 36 months of follow-up/study baseline.

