### Primary outcomes

The two primary outcomes PRolaCT aims to evaluate are:
Health-related quality of life after 12 months of follow-upDisease remission after 36 months of follow-up

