### Sample size calculation

To detect a difference in remission rate at 36 months of 40% between surgery (expected rate 90%) and medical treatment (expected rate max. 50%), with a power of 0.8 and an *α* of 0.025, 55 patients per treatment group arm are needed, when considering that max. 30% in the interventional arm will not undergo surgery. However, to detect a difference of 10 points at the SF-36 mental health scale at *T* = 12 with an *α* of 0.025 and a power of 0.8, assuming that the standard deviation is 16, based on the general population [31], and that max. 30% of the interventional arm does not undergo surgery, at least 101 patients per treatment arm are needed. To compensate for the loss to follow-up, it is aimed to include 110 patients per treatment arm and therefore 220 patients in total per RCT/PRolaCT-O (aiming for at least 110 patients per treatment group in PRolaCT-O). If patient recruitment would prove challenging, and the required sample size for separate analyses of the RCTs cannot be reached for two or more of the RCTs (PRolaCT-1, PRolaCT-2, or PRolaCT-3) within the duration of the study, the planned analyses could be performed using the combined sample size for two to three RCTs of 220 patients.

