### Planned statistical analyses

We intend to perform all statistical analyses separately for PRolaCT-O and PRolaCT-1, PRolaCT-2, and PRolaCT-3. However, a combined analysis of two to three RCTs may be performed, as stated above, using a regression analysis with adjustment for randomisation group type. A post hoc meta-analysis including all three RCTs and PRolaCT-O will be performed, whatever the course of the study.

To account for positive results due to multiple testing, a lower than usual *p*-value, i.e. < 0.02, will be considered statistically significant. All statistical analyses will be performed according to the intention-to-treat principle. In a sensitivity approach, a per-protocol analysis will also be performed, which may be of added value in case many patients, after consultation, decide not to be operated.

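### The two primaries are sized at alpha 0.025 each but tested at a fixed p < 0.02; Holm at a family-wise 0.05 would match the sizing alpha and give the SF-36 mental health comparison more power

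*Protocol article*

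**What the plan says.** The abstract's Background hypothesises that "early or upfront surgical resection is superior to DA treatment both in terms of HRQoL and remission rate". The main-text Background puts the hypothesis without the word both, saying that the surgical "treatment is superior to standard care (DA treatment) for patients with a visible prolactinoma of limited size", and then numbers two primary outcome parameters. The Primary outcomes section repeats the pair: "The two primary outcomes PRolaCT aims to evaluate are" HRQoL at 12 months and remission at 36 months.

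The Sample size calculation handles the two outcomes separately. Remission is sized at an alpha "of 0.025, 55 patients per treatment group arm are needed", and the MHS at an alpha "of 0.025 and a power of 0.8, assuming that the standard deviation is 16", which gives 101 per arm. Recruitment is set at 110 per arm to cover loss to follow-up.

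Planned statistical analyses then reads "To account for positive results due to multiple testing, a lower than usual" p-value, "i.e. < 0.02, will be considered statistically significant". The sentence is not limited to the primaries. Under Main endpoints, MHS is compared by linear regression adjusted for baseline and remission by a chi-square test. No step-down or alpha-recycling procedure is given.

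**The concern.** Two things do not fit well. First, the sample size was set with one per-endpoint alpha (0.025) and the results will be judged with another (0.02). The outcome that drives the sample size is therefore tested more strictly than it was powered for.

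Second, once the two primaries are read as separate claims, a fixed reduced alpha for each is not the most powerful way to hold the family-wise error. Holm holds the same bound and never rejects less. Remission has far more power than MHS at the planned size, so in most trials the alpha reserved for remission would become available for MHS. MHS is the harder endpoint to win, and the Discussion says recruitment has been limited.

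**Working it through.** **Inputs.** From the Sample size calculation: remission 90% with surgery and 50% with medical treatment; MHS difference 10 points, SD 16; 30% of the intervention arm not operated; power 0.80; alpha 0.025; 101 and 110 per arm. The threshold of 0.02 is from Planned statistical analyses. The article gives neither the correlation between the two endpoints (taken as 0 to 0.5) nor that between baseline and 12-month MHS (taken as 0.3 to 0.6).

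**1. Reproduce the stated sizes.** Dilution by 30% gives remission 0.7 × 0.90 + 0.3 × 0.50 = 0.78 against 0.50, and an MHS difference of 0.7 × 10 = 7.

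- Remission, two-sided 0.025, pooled variance, mean rate 0.64: n = [2.2414 × √(2 × 0.64 × 0.36) + 0.8416 × √(0.78 × 0.22 + 0.50 × 0.50)]² / 0.28² = (1.5215 + 0.5465)² / 0.0784 = 54.5, so **55**, as stated.
- MHS, two-sided 0.025: n = 2 × (2.2414 + 0.8416)² × (16/7)² = 99.3, so 100. With the t distribution, power is 0.797 at 100 and 0.802 at 101, so **101**, as stated.

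One-sided 0.025 would give 45 and 83, so the sizing alpha is two-sided 0.025. That is half of 0.05, although the article does not call it a split.

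**2. MHS power at the stated threshold.** Noncentrality is 7 / (16 × √(2/n)), which is 3.109 at 101 and 3.245 at 110. Unadjusted power is Φ(noncentrality − z), with z = 2.326, 2.241 and 1.960:

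| n per arm | 0.02 | 0.025 | 0.05 |
|---|---|---|---|
| 101 | 0.783 | 0.807 | 0.875 |
| 110 | 0.821 | 0.842 | 0.901 |

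The t distribution gives 0.777, 0.802 and 0.872 at 101. At 0.02 the normal formula needs 2 × (2.3263 + 0.8416)² × (16/7)² = 104.9, so 105 per arm. Remission power at 0.025 is 0.977 at 101 and 0.985 at 110.

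**3. Holm at a family-wise 0.05** (smaller p-value at 0.025; if rejected, the other at 0.05). MHS is rejected if its p-value is below 0.025, or if it is below 0.05 and remission is below 0.025. For independent endpoints:

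- 101 per arm: 0.807 + 0.977 × (0.875 − 0.807) = **0.873**
- 110 per arm: 0.842 + 0.985 × (0.901 − 0.842) = **0.900**

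At an endpoint correlation of 0.5, simulation gives 0.872 and 0.899, so the assumption hardly matters.

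**4. Split the gain by source.** At 101: 0.783 to 0.807 from relaxing 0.02 to 0.025 (2.4 points), then 0.807 to 0.873 from Holm (6.6 points). At 110: 2.1 points, then 5.8. If the family were held at 0.04 instead (Holm at 0.02, then 0.04), MHS power would be about 0.852 at 101 and 0.882 at 110.

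**5. Allow for the planned baseline adjustment.** Adjustment multiplies the SD by √(1 − r²). At r = 0.5 and 101 per arm, noncentrality is 3.109 / 0.866 = 3.590. Power is then 0.897 at 0.02, 0.911 at 0.025, and 0.948 under Holm, so Holm adds about 4 points. At r = 0.3 it adds about 6 points (0.846 to 0.902), and at r = 0.6 about 2 (0.950 to 0.972).

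**6. Family-wise error.** Two tests at 0.025: at most 0.05. Two at 0.02: at most 0.04. Holm as above: at most 0.05.

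**The case against.** The strongest reply is that nothing here is invalid. Two tests at 0.02 hold the family-wise error at or below 0.04, the stated sizes are correct for alpha 0.025, and a more powerful alternative does not make a plan wrong. That stands: the point concerns efficiency and consistency, not error control. Nor is the shortfall at 0.02 certain to occur. At the full 110 per arm unadjusted power is 82%, and baseline adjustment with a correlation of only 0.3 gives about 82% at 101 per arm.

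A comparison of 78% with 87% also mixes two changes, since it sets a family held at 0.04 against one held at 0.05. That too stands, so step 4 separates them.

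A reader might go further and infer from the abstract's word both that success needs both endpoints, that the reduced alpha contradicts this, and that a split result has no defined verdict. The documents do not support that. The phrase sits in a background sentence and sets no success rule. The main-text hypothesis omits it, the outcomes are numbered separately, each is sized and tested on its own, and one threshold applies to both. So each endpoint has a verdict when they disagree. On the article's inputs, exactly one is significant at 0.02 in about 21 to 23% of trials at 101 per arm and 17 to 19% at 110: not rare, but not the expected result. If both were in fact required, Holm would not be the remedy; each could be tested at 0.05.

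**Conclusion.** The point holds as a matter of consistency and efficiency. The sizing alpha (two-sided 0.025 each) and the analysis threshold (0.02) differ, which takes unadjusted MHS power at 101 per arm from the planned 80% to about 78%. For two separate claims, Holm at a family-wise 0.05 restores the sizing alpha and raises MHS power to about 87% at 101 per arm and 90% at 110. Like for like, Holm itself adds about 7 points at 101 and 6 at 110, and about 4 at 101 under the planned adjusted analysis if the baseline correlation is 0.5.

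These figures rest on the article's design inputs, on 30% non-surgery in the intervention arm, and on remission being the easier endpoint. If remission failed at 0.025, no alpha would pass to MHS and Holm would give the same MHS result as a fixed 0.025. The mismatch between the abstract's wording and the main text is a wording note only.

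**What to change.** In Planned statistical analyses, replace the fixed p < 0.02 for the two primaries with Holm at a family-wise 0.05 within each RCT: the smaller p-value is tested at 0.025 and, if it is rejected, the other at 0.05. Say separately which threshold, if any, applies to the secondary outcomes, because the present sentence covers everything. State that the two primaries support separate claims, and reword the abstract's hypothesis to agree with the main-text Background.

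This needs no extra patients or data. Its one practical cost is timing: an MHS p-value at or below 0.025 can be declared at month 12, but one between 0.025 and 0.05 cannot be called significant until the 36-month remission result is known. The family-wise bound also moves from 0.04 to 0.05, in line with the alpha used for sizing.

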**Methods:**

We present a combined randomised clinical trial and observational cohort study design, which comprises three unblinded randomised controlled trials (RCTs; PRolaCT-1, PRolaCT-2, PRolaCT-3), and an observational study arm (PRolaCT-O) that compare neurosurgical counselling, and potential subsequent endoscopic transsphenoidal adenoma resection, with current standard care. Patients with a non-invasive prolactinoma (< 25 mm) will be eligible for one of three RCTs based on the duration of pre-treatment with DAs: PRolaCT-1: newly diagnosed, treatment-naïve patients; PRolaCT-2: patients with limited duration of DA treatment (4–6 months); and PRolaCT-3: patients with persisting prolactinoma after DA treatment for > 2 years. PRolaCT-O will include patients who decline randomisation, due to e.g. a clear treatment preference. Primary outcomes are disease remission after 36 months and HRQoL after 12 months.

**Discussion:**

Early or upfront surgical resection for patients with a limited-sized prolactinoma may be a reasonable alternative to the current standard practice of DA treatment, which we will investigate in three RCTs and an observational cohort study. Within the three RCTs, patients will be randomised between neurosurgical counselling and standard care. The observational study arm will recruit patients who refuse randomisation and have a pronounced treatment preference. PRolaCT will collect randomised and observational data, which may facilitate a more individually tailored practice of evidence-based medicine.

**Trial registration:**

US National Library of Medicine registry (ClinicalTrials.gov) NCT04107480. Registered on 27 September 2019, registered retrospectively (by 2 months).

**Supplementary Information:**

The online version contains supplementary material available at 10.1186/s13063-021-05604-y.

## Administrative information

Trial registration

Primary identifying number:

CCMO-Registry ID: NL63919.058.18

Secondary identifying numbers:

ZonMw Grant ID: 843002806

ClinicalTrials.gov ID: NCT04107480

Protocol version: 5

Issue date: 7 Jan 2021

Protocol amendment number: 3

Trials Sponsor (coordinating centre): Leiden University Medical Center

## Background

Prolactin-producing pituitary adenomas typically cause functional hyperprolactinaemia, which is characterised by galactorrhoea and hypogonadism, and may therefore result in subfertility [1]. Additionally, non-specific symptoms, such as fatigue, and psychological and neurocognitive complaints have been described [1]. Although a rare condition, prolactinomas account for over half (32–66%) of all pituitary adenomas [1]. Prolactinomas are found 3 times more frequent in women than in men with a peak incidence between the age of 25 and 35 years [2, 3]. The majority of prolactinomas are subcategorised, based on the size on magnetic resonance imaging (MRI), as microprolactinomas (< 10 mm; 80%), but they may also present as macro (10–40 mm) or giant (> 40 mm) and invasive tumours, which may compromise visual function due to compression of the optic chiasm, nerves, or tracts [2].

Prolactinoma treatment is primarily targeted at reduction of symptoms and restoration of gonadal status and fertility by normalising prolactin levels [4]. As it is a highly effective and non-invasive treatment option, medical treatment with a dopamine agonist (DA) is recommended as first-line treatment for almost all prolactinoma patients, while endoscopic transsphenoidal resection is reserved for those patients with (severe) DA intolerance or in case of DA-resistant prolactinoma [4].

Although DA treatment results in normalisation of prolactin levels, and subsequent reduction of symptoms in 81% of patients, the 2-year remission rate after DA withdrawal remains low (34%) and, therefore, long-term medical treatment should be expected [5]. DA treatment is usually well tolerated, although orthostatic hypotension and gastrointestinal complaints are frequently reported as side effects. DAs are furthermore associated with psychological side effects, which are mild in 40%, but more severe in up to 5–10% of patients [5–13]. Particularly, impulse control disorders (ICDs), e.g. pathologic gambling, are acknowledged as a typical side effect [13–16]. The heterogenous pattern of side effects and prolactinoma symptomatology may (in part) explain that both untreated (symptomatic) and medically treated prolactinoma patients have reported a decreased physical and mental health-related quality of life (HRQoL) [5, 17–22].

Although clearly more invasive, endoscopic pituitary surgery has a well-established good safety profile for prolactinomas of limited size. Long-term morbidity from complications occurs in less than 2–3% of patients (mostly due to hypopituitarism or permanent diabetes insipidus), whereas transient perioperative complications, such as cerebrospinal fluid leakage and transient diabetes insipidus, occur in less than 5 and 15% of patients, when surgery is performed by experienced neurosurgeons [5, 17, 23–27]. Resulting in immediate cure in 80 to 90% of prolactinoma patients, endoscopic transsphenoidal surgery is also a highly effective treatment [5, 17, 23–25]. Moreover, the vast majority of postoperative patients will not need long-term DA treatment, since recurrence rates after surgery are 4–15% [5, 17, 28]. Interestingly, two recent simulation studies have estimated that endoscopic surgery could be a more cost-effective treatment when compared to cabergoline, the most effective DA [29, 30].

With improvement of the endoscopic transsphenoidal surgical technique, increasing evidence of potentially detrimental side effects of DAs, and disappointing remission rates after a period of at least 2 years of DA treatment, equipoise may exist for these treatment options, particularly for patients with the greatest likelihood for successful complete adenoma resection (i.e. clearly visible, of limited size, and non-invasive tumours). Nevertheless, the efficacy-to-safety ratios of surgery and medical treatment are highly different and incomparable, so HRQoL after surgery (without DA in most cases) and risk of complications should be weighed against HRQoL during (often long-term) medical treatment and its potential side effects. However, there are currently only a handful of retrospective observational studies published on this topic with major drawbacks, such as selection bias and insufficient and inappropriate correction for confounding variables [5]. Therefore, we believe that this is the right moment in time to perform a randomised controlled trial (RCT) comparing both treatment strategies.

We hypothesise that endoscopic transsphenoidal adenoma resection as a first-line, or equally valid second-line, treatment is superior to standard care (DA treatment) for patients with a visible prolactinoma of limited size (< 25 mm, no tissue invasion). The primary outcome parameters are (1) HRQoL measured after 12 months of follow-up (i.e. 12 months after randomisation or, in PRolaCT-O, study baseline) and (2) the proportion of patients in remission at 36 months of follow-up/study baseline.

## Methods

### Study design

This combined randomised clinical trial and observational cohort study design comprises three unblinded parallel superiority prolactinoma RCTs (PRolaCT-1, PRolaCT-2, PRolaCT-3) and an observational study arm (PRolaCT-O) that will compare counselling for endoscopic transsphenoidal adenoma resection to standard care (DA treatment) in patients with a prolactinoma of limited size (i.e. < 25 mm, no tissue invasion):
PRolaCT-1 compares counselling for surgical resection as a first-line treatment in newly diagnosed, treatment-naïve prolactinoma patients.PRolaCT-2 compares counselling for surgical resection as an early second-line treatment in patients who have had DA treatment for a limited time period (4–6 months).PRolaCT-3 compares counselling for surgical resection as an equal second-line treatment in patients who have persisting prolactinoma, i.e. recurring hyperprolactinaemia and persisting pituitary adenoma on MRI, after DA treatment for a long period of time (> 2 years).PRolaCT-O evaluates counselling for surgical resection as an equally valid second-line treatment and standard care in an observational study setting, aiming to include all patients eligible for PRolaCT-1, PRolaCT-2, and PRolaCT-3 who do not participate in the RCTs because of a strong patient and/or physician treatment preference, and/or because the patient does not consent to randomisation.

All interventions and study procedures are otherwise identical for the three RCTs and the observational cohort.

Since some patients will be unwilling to be randomised for various reasons, such as a strong preference for either surgery or DA treatment, there is a risk that for the RCT a selected subpopulation is recruited, excluding patients with more pronounced side effects of DA treatment or those with an adenoma that is expected to be relatively difficult to resect completely. Especially outcomes in HRQoL might be attenuated or overestimated and there is a risk that the results cannot be generalised to all prolactinoma patients. The PRolaCT-O observational arm was added to provide a fall-back mechanism for evaluation of primary and secondary study objectives in case recruitment would prove to be challenging and to provide data for the evaluation of a possible selection bias in the RCTs, and is designed to collect real-life data about the eligible cohort. The combined RCT and observational cohort approach was received well by our advisory board (including a patient representative) and better reflects clinical decision-making in real life, as the MDT or treating physician may also have a preference due to tumour- and patient-specific characteristics. Furthermore, the prospective data collection of PRolaCT-O includes comprehensive information about expected confounders, such as duration and effectiveness of prior DA treatment, the amount and severity of side effects of DA treatment, and expected difficulty of surgery as judged by two blinded neurosurgeons.

#### Study setting

Endoscopic surgery is centralised in a few tertiary expert neurosurgical centres, while endocrine care for prolactinoma is delivered by endocrinologists and gynaecologists in all hospitals. For an expected enrolment period of 3 years, starting June 2019, recruitment for PRolaCT operates from five participating neurosurgical reference centres and uses regional multidisciplinary networks to recruit patients from the referring hospitals. PRolaCT is furthermore intended to expand to other reference centres in the Netherlands and internationally to the UK, France, and Germany, in collaboration with European Networks.

### Study population

Eligibility to participate with one of the RCTs or PRolaCT-O is based on the following inclusion and exclusion criteria.

#### Inclusion criteria

At least 18 years of ageA history of signs and symptoms matching with prolactinomaHyperprolactinaemia, defined as a prolactin level ≥2 times the local laboratory maximum, present at the time of enrolment (PRolaCT-1) or present < 12 months before enrolment (PRolaCT-2 and PRolaCT-3)No clear alternative explanation for hyperprolactinaemia, e.g. medication usePresence of a clearly identifiable pituitary mass on MRI not invading the cavernous sinus and with a maximum diameter ≤25 mm. A representative MRI at the time of randomisation is required. This MRI should generally not be older than 12 months in PRolaCT-3 and 2 months in PRolaCT-1 and PRolaCT-2Defining inclusion criteria for the three RCTs are:
PRolaCT-1: no prior prolactinoma treatmentPRolaCT-2: prior DA treatment for 4–6 months orPRolaCT-3: prior DA treatment for at least 2 years and having conducted at least one withdrawal attempt within 12 months prior to study recruitment (if the withdrawal attempt took place > 6 months before study inclusion, another withdrawal attempt is performed before randomisation to confirm prolactinoma persistence)

